#### Caregiver strain

Data on the Modified Caregiver Strain Index [20] was obtained from 25 next-of-kin at 12 weeks post-injury and 21 next-of-kin at 26 weeks post-injury. Given the relatively small sample size for these data, differences in caregiver strain between the control and intervention phases of the trial will be assessed using independent samples *t*-tests. The *t*-tests will be conducted at the 5% significance level, and 95% confidence intervals will be reported. No additional modelling will be undertaken and no adjustments for any covariates will be made.

#### Anxiety and depression

Separate linear mixed effects regression model will be used to assess between-condition differences on anxiety and depressions scales of the HADS [21]. Time period, age at recruitment, injury type and severity (dichotomised mRS [18] at baseline) will be controlled for as fixed effects in the models. Recruitment site and participant/individual will be included as random effects. In addition, time since injury and the interaction of time since injury with condition (control/intervention) will be included in the models. The interaction effect will be used to assess the between-group differences at 12 weeks post-injury [H5.3] and at 26 weeks post-injury [H5.4].

### Safety assessments

Adverse events (AEs) are classified as possibly, probably or definitely attributable to the intervention. Serious adverse events (SAEs) are classified as not related, unlikely, possibly, probably or definitely attributable to the intervention as they occur (between consent and 26 weeks post brain injury). AEs and SAEs will be reported by condition (control/intervention) in the main paper. The structure of this table is presented in Table 6 of Appendix.

AEs and SAEs possibly, probably or definitely attributable to the intervention are expected to be rare. Therefore, no formal hypotheses are associated with these. As rare events, AEs and SAEs are expected to have a Poisson or a negative binomial distribution. If the data suggests that there is a between-condition difference of more than 3 standard deviations in AEs or SAEs, the distribution will be modelled, and an appropriate generalised linear model will be developed to assess between-condition differences.

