## Changes since the commencement of the trial

### Recruitment rate

Recruitment remained below the anticipated rate throughout the trial. This was due to a number of issues including:The COVID-19 pandemic from 2020 to the trial close;Difficulty experienced in recruitment of people with TBI;A hiatus in the recruitment of participants incapable of independent consent, i.e. discontinuation of approval to gain consent by proxy from 2018 to 2020 as part of the Western Australian Guardianship and Administration Amendment (Medical Research) Act 2020 [38];Initial ethical approval for recruitment within hospital setting only—participants were often discharged before being recruited; even after approval was gained to recruit within the community, this remained problematic as many were rural residents, and recruiting remotely proved to be challenging; andLimited availability of recruiters in some hospitals at times, e.g. staffing shortages.

All assessments in this trial were designed to be undertaken remotely or in person and are validated for remote administration. Similarly, the Aboriginal Brain Injury Coordinator services were able to be undertaken via telephone and telehealth, as planned. Therefore, COVID-19 pandemic, which was declared as a global pandemic on March 23, 2020, did not affect the administration of the trial for recruited participants. Recruitment concluded on 31 July 2021, as planned. The total number of patients recruited was 108 with uneven distribution across sites and clusters. The numbers recruited by site/cluster per time period are presented in Table 7 in Appendix.

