**System-level outcomes**			
Minimum Processes of Care Achieved (Yes)			
Occasions of Service

**Table 6 Tab6:** Adverse events and serious adverse events

	**Control**	**Intervention**	**All**
	*n* (%)	*n* (%)	*n* (%)
No. of adverse events (AEs)			
Neurological complications			
0			
1			
2			
> 2			
No. of serious adverse events (SAEs)			
0			
1			
2			
> 2

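### A between-condition safety model is fitted only past an undefined 3 SD difference, so a large SAE excess could go without an estimate or interval, and the AE classes do not suit a comparison by condition

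*SAP article*

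**What the plan says.** The Safety assessments section of the SAP article makes four relevant statements.

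- Reporting is unconditional: "AEs and SAEs will be reported by condition (control/intervention) in the main paper". The shell is Table 6 of the Appendix, with n (%) columns by condition and rows for 0, 1, 2 and more than 2 events.
- There is no test plan. Attributable events are expected to be rare, and "Therefore, no formal hypotheses are associated with these".
- Modelling is conditional. The section says that "AEs and SAEs are expected to have a Poisson or a negative binomial distribution", and that a generalised linear model follows if the data suggest that "there is a between-condition difference of more than 3 standard deviations in AEs or SAEs, the distribution will be modelled".
- The two event types have different relatedness scales. For AEs: "Adverse events (AEs) are classified as possibly, probably or definitely attributable to the intervention". For SAEs: "Serious adverse events (SAEs) are classified as not related, unlikely, possibly, probably or definitely attributable to the intervention as they occur".

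Three other places bear on this. Analysis principles and general considerations promises a 95% confidence interval with every treatment-effect estimate. Interim analysis describes the data and safety monitoring committee's guide, which compares numbers of SAEs and uses 3 standard errors. Other participant-level data says that AEs and SAEs during enrolment were recorded when notified, with no limit by phase or attribution.

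**The concern.** Whether the final report contains an estimated safety difference depends on how large the observed difference is. A limit of three standard errors makes sense as a guide for stopping a running trial. At final analysis no stopping decision remains to protect, and the limit only decides whether readers get an estimate with its uncertainty. A moderate or even large excess of SAEs would appear as two columns of counts, with no rate ratio and no interval.

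The rule also cannot be applied reproducibly. Two analysts could choose different scales and different standard deviations and reach opposite decisions about fitting the model. The phases may differ in size, and observation time differs between participants, so the choice of denominator matters.

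For AEs the difficulty is different. If the classification is taken literally, every AE is at least possibly due to the intervention. A contrast between phases would then largely reflect the definition and not harm.

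**Working it through.** **Inputs.** From the SAP: the 3 SD threshold, the Poisson or negative binomial expectation, and 108 participants ("The total number of patients recruited was 108 with uneven distribution across sites and clusters"). The safety section gives no event rate, power or sample size, so there is no figure of the plan to reproduce. The split by condition is not in the text at hand. Assumed: 54:54, with a range of 36:72 to 72:36 (control:intervention); 10% to 30% of control participants with an SAE, or 0.25 to 1.0 SAEs per participant.

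**Reading A: 3 SD means 3 standard errors of a Poisson difference, at equal exposure.** With a control and b intervention events, the gate opens when b − a > 3√(a + b). A normal deviate of 3 has two-sided p = 0.0027.

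| Control events a | Smallest b that opens the gate | Check |
|---|---|---|
| 0 | 10 | 10 > 3√10 = 9.49; 9 is not > 3√9 = 9 |
| 2 | 15 | 13 > 3√17 = 12.37 |
| 5 | 21 | 16 > 3√26 = 15.30 |
| 8 | 26 | 18 > 3√34 = 17.49 |

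For 5 v 20, the difference is 15 and 3√25 = 15, which is not more than 3, so no model is fitted. The exact binomial p for 20 of 25 is 0.0041. The rate ratio is 20/5 = 4.0, with 95% CI 1.5 to 13.6 from the exact binomial limits. This example lies on the boundary; 5 v 19 falls inside it (14 < 3√24 = 14.70) at a ratio of 3.8.

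**Chance that the gate opens, for the share of participants with an SAE.** Take 20% v 40% at 54:54. The standard error under no difference is √(2 × 0.3 × 0.7/54) = 0.0882. Under the alternative it is √((0.2 × 0.8 + 0.4 × 0.6)/54) = 0.0861. The probability is Φ((0.20 − 3 × 0.0882)/0.0861) = Φ(−0.75) = 0.23. With 1.96 in place of 3 it is 0.62. For 10% v 20% the figures are 0.06 and 0.31. Over splits from 36:72 to 72:36, 20% v 40% gives 0.16 to 0.24.

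**Reading B: 3 SD means the SD of per-participant counts.** For a Poisson mean m, the intervention mean must exceed m + 3√m. The ratio (m + 3√m)/m is 7.0, 5.2 and 4.0 at m = 0.25, 0.5 and 1.0. On this reading the gate would almost never open.

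**Why the unstated scale matters.** Suppose the true rates are equal at 0.5 SAEs per participant and the split is 36:72. Applied to raw counts, the 3-SE rule flags an excess in the larger phase with probability 0.28; applied to rates, it flags either direction with probability of about 0.003. Suppose instead that the rate truly doubles from 0.5 and the split is 72:36. Counts flag the harm with probability 0.001, rates with probability 0.50. The SAP does not say which scale applies. Observation time also varies: SAEs run from consent to 26 weeks post-injury and recruitment falls within weeks 0 to 6, so a completer is observed for 20 to 26 weeks.

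**AEs.** If only attributable AEs are counted and the control phase has none, 10 events in the intervention phase open the gate under Reading A (first row of the table). The model then fitted has no finite maximum-likelihood rate ratio, because the control count is zero.

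**The case against.** The strongest reply is that the plan already shows the safety data. A reader might infer that no safety comparison is made unless the trigger is met. The SAP does not support that: reporting by condition is unconditional, Table 6 carries n (%), and a 5 v 20 split would be visible there. Only the model, with its estimate and interval, is gated.

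A reader might also infer that the rule compares raw counts. The Safety assessments section never says so. The wording about numbers of SAEs belongs to the monitoring committee's guide under Interim analysis, and a generalised linear model of the kind foreseen could include an exposure offset. What stands is that the scale is unstated.

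Thirdly, a reader might conclude that AEs cannot occur in the control phase. That is an inference. Other participant-level data describes recording during enrolment without limit by attribution, and Table 6 has a Control column for AEs. What stands is that these places do not agree with the AE classification sentence. Opening the gate would in any case only cause a model to be fitted; it would not declare harm.

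Finally, descriptive safety reporting is defensible in a trial of 108 participants with no formal safety hypotheses. That is granted, but estimation needs no hypothesis. A rate ratio with its interval is itself descriptive, and it shows the uncertainty that counts alone do not.

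**Conclusion.** The concern holds in limited form. The modelled safety comparison depends on an observed difference above an undefined 3 SD, with no scale or denominator stated, and the term differs from the standard errors used under Interim analysis. Read as 3 standard errors of a Poisson difference, the gate would leave a fourfold SAE excess of 5 v 20 without an estimate. It would open with probability of about 0.23 for a doubling from 20% to 40% of participants. Read as the SD of per-participant counts, it would almost never open. The AE classification fits poorly with the recording statement and with a comparison by condition. How far the control AE count is depressed cannot be settled from the SAP.

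These sizes rest on assumed event counts, SAE rates and phase splits. The statement about uneven recruitment concerns sites and clusters, so it does not itself show unequal phases. The primary analysis is unaffected. This is an inexpensive improvement to the safety section.

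**What to change.** 1. Delete the 3 SD trigger from Safety assessments. The different term used for monitoring under Interim analysis then no longer needs reconciling with a final-analysis threshold.
2. Always report all-cause SAEs, across all five relatedness classes, by condition. Give the number of participants and total follow-up time as denominators, and a rate ratio with 95% CI from a Poisson or negative binomial model with log follow-up time as offset. Use an exact interval if events are sparse. Label the result descriptive, because control time precedes intervention time at every site and a simple rate ratio is not protected from calendar trends.
3. Reconcile the AE classification with Other participant-level data and Table 6. Compare AEs between conditions only if they were recorded irrespective of attribution in both phases; otherwise list attributable AEs descriptively.

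The cost is a few sentences in the SAP and one simple model. No new SAE data are needed; the follow-up time requires dates of consent and injury and of any death or withdrawal, which the trial should already hold because its visits are timed from injury. The drawback is a wide interval when events are few.

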## Changes since the commencement of the trial

### Recruitment rate

Recruitment remained below the anticipated rate throughout the trial. This was due to a number of issues including:The COVID-19 pandemic from 2020 to the trial close;Difficulty experienced in recruitment of people with TBI;A hiatus in the recruitment of participants incapable of independent consent, i.e. discontinuation of approval to gain consent by proxy from 2018 to 2020 as part of the Western Australian Guardianship and Administration Amendment (Medical Research) Act 2020 [38];Initial ethical approval for recruitment within hospital setting only—participants were often discharged before being recruited; even after approval was gained to recruit within the community, this remained problematic as many were rural residents, and recruiting remotely proved to be challenging; andLimited availability of recruiters in some hospitals at times, e.g. staffing shortages.

All assessments in this trial were designed to be undertaken remotely or in person and are validated for remote administration. Similarly, the Aboriginal Brain Injury Coordinator services were able to be undertaken via telephone and telehealth, as planned. Therefore, COVID-19 pandemic, which was declared as a global pandemic on March 23, 2020, did not affect the administration of the trial for recruited participants. Recruitment concluded on 31 July 2021, as planned. The total number of patients recruited was 108 with uneven distribution across sites and clusters. The numbers recruited by site/cluster per time period are presented in Table 7 in Appendix.

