### Study design

Healing Right Way was planned as a stepped wedge trial with four steps over 3 years. Eight sites (four rural hospitals and four urban sites) are participating in the trial. The 3-year timeframe was divided into six 26-week periods. At the start of the trial, all sites were in the control condition which contributed a baseline measurement for all sites. The trial plan called for two sites cross over to the intervention condition, at the end of the first 26-week period, while the other sites remained in the control condition. At the end of the second 26-week period, two additional sites were to cross over from the control condition to the intervention condition, and at the end of the third 26-week period, the last two sites were to cross over to the intervention condition. Starting with the fifth 26-week period, all sites were to be in the intervention condition. The trial design allowed for one additional 26-week period in which all sites were to be in the intervention condition. We recruited fewer people than anticipated—especially in the initial periods after the trial commenced. The trial design was therefore modified to accommodate the reduced recruitment numbers. On advice of the Trial Management Committee, the trial design maintained four steps as planned, but the baseline extended period by an additional 26 weeks. The modified design is presented in Fig. 1.

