### Recruitment and allocation of participants

The trial used a continuous recruitment strategy [23, 24]. All eligible participants who presented to a participating site in the trial period were invited to participate. Participants who accepted the invitation were allocated to the trial intervention phase (control or intervention) that the site was undergoing at the time of their recruitment.

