## Statistical analysis plan

### Analysis principles and general considerations

All outcomes and analyses were prospectively characterised as primary or secondary.This is a superiority trial with intervention expected to yield superior outcomes, compared to control. However, all outcomes will be tested independently at the two-tailed 5% significance level. All estimates of treatment effects will be presented with 95% confidence intervalsNo formal adjustments will be undertaken to constrain the Type I error associated with planned secondary or exploratory analyses. The information provided by analyses is designed to supplement the evidence from the primary analyses; it will provide a more complete characterisation of the treatment effects.The analyses for all quantitative outcome measures will be conducted on an intention the treat (ITT) basis, i.e. all participants will be analysed in the trial phase (control or intervention) in which they were recruited, regardless of whether their treatment adhered to the trial protocol or not. The ITT strategy for this trial is based on the following principles:◦ All available outcome data are collected on all recruited participant◦ For the ITT analysis, the outcomes for each participant will be included in the data for the trial phase (control/intervention) in which the participant was recruited.◦ All available outcome data will be used in the primary analyses. The primary analyses will be reported without imputation of missing data. If the amount of missing data exceeds 10% at the primary endpoint, missing data will be imputed under the assumption that data is missing at random.◦ A sensitivity analysis including all randomised individuals will be conducted. The sensitivity analysis will consider alternative assumptions about data missing not at random (MNAR).For primary and secondary analyses, the treatment effects for the participant-level effectiveness outcomes will be adjusted for brain injury type (stroke or TBI) and severity of injury (mRS) [18] at baseline. In addition, age at recruitment, timepoint (time since injury) and time period (6-month block of time in which the participant is recruited to the step-wedge trial) will be included as fixed effects. Hospital site will be included as a random effect. Unadjusted analyses will be reported separately from these pre-specified analyses.All analyses will be conducted using the R Statistical Programming Language [32] after data collection is completed and the database is locked.

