#### Analysis

A mixed effects linear regression model will be used to assess the between-group difference on Euro QOL–5D-3L [17] VAS score at 26 weeks post-injury. The model will control for injury type and severity (dichotomised mRS [18] at baseline), age at recruitment and time period (time since commencement of the trial) as fixed effects; recruitment site and participant/individual will be included as random effects. The treatment effect will be reported as the mean difference between the intervention condition and the control condition, together with the 95% confidence interval for the difference.

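### A gap in proxy consent shifts case mix with calendar time, and the SAP neither fixes the time term that would absorb the shift nor keeps that term in its fallback

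*SAP article*

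**What the plan says.** The section Recruitment rate lists, among the reasons for low accrual, "A hiatus in the recruitment of participants incapable of independent consent", explained as "discontinuation of approval to gain consent by proxy from 2018 to 2020". It gives years but no months, and no count of participants enrolled by proxy. The same section says "Recruitment concluded on 31 July 2021, as planned".

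Phase is tied to the calendar. All sites began in control. In Study design, "The 3-year timeframe was divided into six 26-week periods", and after slow accrual "the trial design maintained four steps as planned, but the baseline extended period by an additional 26 weeks". Participants were "allocated to the trial intervention phase (control or intervention) that the site was undergoing at the time of their recruitment".

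Time is described in two ways. Analysis principles and general considerations has "time period (6-month block of time in which the participant is recruited to the step-wedge trial". The primary-outcome Analysis section has "time period (time since commencement of the trial) as fixed effects", and the Abstract likewise refers to time since commencement. No section states whether time is categorical or linear. The secondary mixed models name time period without further definition.

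Case mix is otherwise adjusted through injury type, age and baseline mRS dichotomised at 0–2 versus 3–6. Consent route appears in no model and not in Table 3. Sensitivity analyses covers only departures from missing at random. If a model does not converge, Effect of lower sample size on statistical analysis plan removes time period first and mRS second.

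**The concern.** The gap affects more than the recruitment rate: it also changes the eligible population part-way through a design in which control precedes intervention at every site. People who cannot consent for themselves are likely to be more impaired, and a two-level mRS places them in one class with all other dependent patients. If they enter mainly in later periods and score lower on the VAS, the intervention phase looks worse for reasons unrelated to the intervention.

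The calendar-time term is the main protection. Two features of the plan weaken it: its form is open in the primary model, and it is the first term given up if a model fails to converge, which the SAP itself expects may happen with 108 participants.

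**Working it through.** The SAP gives no figure for this point to reproduce, so the check asks how much of a calendar shift reaches the treatment effect.

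**Inputs from the SAP.** Four clusters, four steps, two all-control periods, 26-week periods, recruitment to 31 July 2021, 108 participants, ICC 0.08.

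**Assumptions.** Fig. 1 and Table 7 are not available here. I take equal recruitment per cluster-period, and either six periods (start about August 2018) or seven (start about February 2018).

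**Cells.** Control cells are 2+3+4+5 = 14 in both layouts. Intervention cells are 4+3+2+1 = 10 (six periods) or 5+4+3+2 = 14 (seven).

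**Model.** Let y be the share of each period in which proxy consent was available, so that a full step equals 1. The generalised least squares estimate is (M′V⁻¹M)⁻¹M′V⁻¹y. M holds treatment, intercept and the chosen time term. V has (1−ρ)/m on the diagonal plus ρ between cells of one cluster, with ρ = 0.08 and m = 108/24 = 4.5 (or 108/28 = 3.9). The treatment coefficient is the fraction of the step that becomes bias.

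**Proxy consent absent until it returns in February or August 2020:**

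| Layout, return at | Control cells open | Intervention cells open | Raw difference | Blocks | Linear | No time term |
|---|---|---|---|---|---|---|
| 6 periods, period 4 | 3/14 | 9/10 | 0.69 | 0.00 | 0.07 | 0.76 |
| 6 periods, period 5 | 1/14 | 7/10 | 0.63 | 0.00 | 0.12 | 0.70 |
| 7 periods, period 5 | 1/14 | 11/14 | 0.71 | 0.00 | 0.13 | 0.77 |
| 7 periods, period 6 | 0/14 | 8/14 | 0.57 | 0.00 | 0.03 | 0.62 |

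Over ICC 0.01 to 0.15 the linear column spans 0.03 to 0.14 and the last column 0.58 to 0.78. Blocks give exactly zero because a step common to all sites depends on period alone and so lies within the period indicators.

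**Wider timings (ICC 0.08).** These vary both the start and the end of the gap.

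| Layout, gap | Control cells in gap | Intervention cells in gap | Linear | No time term |
|---|---|---|---|---|
| 6 periods, trial start to start of 2020 | 75% | 8% | 0.05 | 0.74 |
| 6 periods, trial start to end of 2020 | 99% | 55% | 0.10 | 0.49 |
| 6 periods, start of 2019 to mid-2020 | 67% | 27% | 0.31 | 0.44 |
| 6 periods, start of 2019 to end of 2020 | 75% | 55% | 0.29 | 0.22 |
| 7 periods, trial start to end of 2020 | 100% | 67% | −0.13 | 0.36 |
| 7 periods, start of 2019 to end of 2020 | 47% | 67% | −0.13 | −0.21 |

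Blocks remain at 0.00 throughout.

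**Scale in VAS points (illustrative assumption).** If 20–30% of recruits after the gap were proxy-consented and scored 15 points lower, the step is 0.20×15 = 3 to 0.30×15 = 4.5 points. In the six-period layout the bias is:
- linear time: 0.05×3 ≈ 0.2 to 0.31×4.5 ≈ 1.4 points;
- no time term: 0.22×3 ≈ 0.7 to 0.74×4.5 ≈ 3.3 points.

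The planned effect is 15 points. These figures precede any correction by baseline mRS.

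**Cost of blocks.** With SD 25 and six periods, the standard error is 8.17 with blocks and 7.92 with linear time: 8.17/7.92 = 1.03.

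**The case against.** The strongest reply is that the plan already handles this. A statewide consent rule is a calendar effect, every mixed model carries a time-period term, and the general principles define that term as a 6-month block for primary and secondary analyses. The wording in the primary model can be read as a loose gloss on the same variable. That stands as far as it goes: with categorical blocks nothing leaks, and even a linear term leaves a modest bias. It does not settle the form, which is nowhere stated, and it does not answer the fallback, which removes the protecting term first.

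A reader might infer that people unable to consent were largely missing from control and present in intervention. The documents do not support that. They give years only. The word discontinuation suggests that proxy approval existed earlier, so early control participants may include such patients. A gap lasting to the end of 2020 would also cover about half or more of the intervention cells.

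A reader might also infer that block effects fail because the shift differed between urban and rural sites. Nothing in the document shows such a difference, and each rural site crosses over together with the urban site that takes its transfers.

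Unadjusted tables carry secular change in any stepped wedge, and the SAP reports unadjusted analyses separately, so that is not a fault specific to this plan.

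**Conclusion.** The concern holds in a limited form. The change in eligible population is documented and is associated with phase under most plausible timings. It is not shown how many participants it affects, and the direction is not certain.

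The plan has no term for consent route, but it does have a time term that removes a common shift entirely if fitted as categorical blocks. The weakness is that this form is not fixed in the primary model and that the term is first to go on non-convergence. The second matters more: about 60–80% of the shift passes through under a February or August 2020 return, against about 3–14% for linear time.

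These fractions rest on equal cell sizes, whereas the SAP reports uneven recruitment, and on an additive shift common to all sites. Blocks would also not reveal a treatment effect that differs in people unable to consent. This is worth correcting, but it does not by itself undermine the primary analysis.

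**What to change.** 1. Define time period once, for all models, as the categorical 6-month recruitment block, and align the Abstract and the primary-outcome Analysis section with it.
2. In the non-convergence rule, do not remove time period first. Keep it when other effects are dropped, and force it into the separate-timepoint models instead of leaving it to AIC selection.
3. Pre-specify a sensitivity analysis of the primary outcome restricted to self-consenting participants, where consent route is recorded, and add consent route by condition to Table 3.

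The cost is wording, one table row and one extra model. Categorical blocks enlarge the standard error by about 3–4%, the fallback has one term fewer to give up, and the restricted analysis will be small and imprecise, so it serves as a check on consistency and not as a test. The SAP does not say that consent route is in the dataset, so the sponsor should confirm this first.
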